**Sociodemographics (EMR, youth, and caregivers)**
Race, ethnicity, sex, education, income, legal history, and placement type
**Pediatric Symptom Checklist (EMR, youth, and caregivers)**
A 35-item measure of child emotional and behavioral problems that has been identified as a feasible method for the early detection of mental health difficulties [46] and intervention outcomes measurement [47]; items are rated as “never present” (0), “sometimes present” (1), or “often present” (2), with the total (summed) score ranging from 0 to 70; for children and youth aged 6 to 18 years, the cutoff score is 28 (≥28=impaired)
**University of California Los Angeles Posttraumatic Stress Disorder Reaction Index for Diagnostic and Statistical Manual of Mental Disorders, Fifth Edition (DSM-5; youth)**
An instrument that screens for exposure to traumatic events and the frequency of posttraumatic stress disorder symptom occurrence during the past month (ranging from 0=none of the time to 4=most of the time) [48]; items map directly onto DSM-5 intrusion, avoidance, and arousal criteria, whereas 2 additional items assess associated features (fear of recurrence and trauma-related guilt); scoring algorithms permit tabulation of the total score as well as B, C, and D subscale scores
**Brief Symptom Inventory (caregivers)**
A 51-item measure of past week mental health symptoms [49]
**Parent-Adolescent General Communication Scale (youth and caregivers)**
A scale that assesses positive and negative aspects of communication via 2 subscales (open family communication and problems in family communication) [50], with 5 items assessing the frequency of communication topics
**Parental Monitoring Questionnaire (youth and caregivers)**
A 24-item measure of parental monitoring across 4 areas or subscales (parental knowledge, child disclosure, parental solicitation, and parental control), with higher scores indicating higher levels of monitoring domains [51]

### Measures

#### Overview

Youth and caregivers in both conditions will each complete the electronic study assessment at baseline and at 1, 3, and 6 months (4 times in total). Unless it is specifically noted, all of the following measures will be collected from youth and caregivers across both conditions. FCFN navigator measures are also included.

#### Primary Outcome Measures

##### Cascade of Care Services

We will collect EMR data that will include (1) percentage screened (for mental health needs), percentage assessed (received full mental health assessment), and percentage in need (determined to meet medical necessity criteria for mental health services); (2) time to screening, full assessment, and determination of need (number of days); (3) percentage referred for mental health treatment as well as percentage who initiated treatment; (4) time to referral and initiation (number of days); (5) whether the youth engaged in treatment (whether they had ≥6 weeks of treatment attendance); (6) number of total mental health treatment sessions completed; (7) sociodemographics (to provide collateral EMR data on race and ethnicity, sex, education, income, legal history, and placement type); (8) Child and Adolescent Needs and Strengths (CANS) screener and full assessment (the number and descriptions of needs and strengths and based on the Diagnostic and Statistical Manual of Mental Disorders, Fifth Edition [DSM-5], diagnosis per the CANS rating and resources manual with regard to children and youth aged 5-18 years); and (9) Pediatric Symptom Checklist score (collected by the specialty mental health provider and entered into the EMR as part of standard clinical and billing practice).

##### Therapeutic Working Alliance

The 12-item Working Alliance Inventory (WAI) [39], which was used in the Cannabis Youth Treatment Study [40], assesses youth perception of therapeutic alliance over time.

##### Navigation Satisfaction Tool, Part I

The 12-item Navigation Satisfaction Tool (NAVSAT), Part I [41], addresses participant satisfaction with navigation services (eg, How satisfied are you with the navigator’s ability to listen or understand your concerns? How satisfied are you with the frequency of contact with the navigator?)

##### Barriers to Care Questionnaire

This 39-item scale (subscales of skills, marginalization, stigma, expectations, knowledge and beliefs, and pragmatics) assesses perceived barriers to youth health care access [43]. Items are rated on the extent of the problem (ranging from 100 for “no problem” to 0 for “very big problem”). Higher scores indicate fewer barriers. The items are at 5.7 grade reading level, and thus youth can complete this questionnaire.

##### Motivation for Youth’s Treatment Scale

This is a psychometrically valid 8-item scale that youth and caregivers complete to measure intrinsic treatment motivation with the subscales of problem recognition and treatment readiness [44].

##### System Usability Scale

The System Usability Scale (SUS) [52] is a 10-item measure that is widely used to evaluate web applications and has proven superior to other measures. The SUS yields a single number representing a composite measure of the overall usability of the system being studied [45]. The SUS scores will be compared with established norms for levels of usability. Our goal is to reach a score of 80, which is in the top 10% of scores, reflects excellent usability, and is associated with recommending the product to a friend (youth and caregivers; intervention group only).

##### Pediatric Symptom Checklist

This 35-item measure of child emotional and behavioral problems [46] is widely used in diverse pediatric primary care settings and has been identified as a feasible method for the early detection of mental health difficulties and intervention outcomes measurement [47]. Items are rated as “never present,” “sometimes present,” or “often present” and scored 0, 1, and 2, respectively. The total (summed) score ranges from 0 to 70; for children and youth aged 6 to 18 years, the cutoff score is 28 (≥28=impaired). We will collect this separately and in addition to available EMR Pediatric Symptom Checklist data to measure changes in symptoms over time (ie, for repeated measures).

##### Brief Symptom Inventory

This 51-item measure will be used to rate the extent to which parents have been bothered in the past week by their own mental health symptoms [49].

##### Texas Christian University Drug Screen 5

This 17-item measure assesses past 12-month quantity and frequency of alcohol and drug use and the perceived level of functioning and impairment associated with substance use (youth only) [53].

##### Parent-Adolescent General Communication Scale

This scale will assess the positive and negative aspects of general communication via 2 subscales (open family communication and problems in family communication) [50]. Five items assess the frequency of communication topics.

##### Parental Monitoring Questionnaire

This 24-item measure is designed to assess parental monitoring across 4 areas or subscales (parental knowledge, child disclosure, parental solicitation, and parental control) [51]. Higher scores indicate higher levels of monitoring domains.

##### Child and Adolescent Services Assessment

This assessment consists of a semistructured interview that obtains information about service use for mental health problems across multiple sectors (eg, juvenile legal system and schools) [54]. Information about the type of facility, the professional discipline of provider or providers, outpatient services, and out-of-home placements is obtained, and the measure has adequate reliability (intraclass correlation coefficient=0.74-0.76). We will categorize the length and nature of treatment received to increase the generalizability of our study results. We will also add items related to participants’ arrest history.

##### University of California Los Angeles PTSD Reaction Index for DSM-5

This instrument is used to screen for exposure to traumatic events and assess the frequency of occurrence of PTSD symptoms in the past month [48]. We will use a modified version of this measure that will only ask about the total number of exposures to traumatic events and not the specific type of event or any details related to the event.

##### Sociodemographics

We will collect data on race, ethnicity, sex, education, income, legal history, and placement type.

##### Number and Types of Contacts

Data regarding the number and types of contacts between the FCFNs and youth and caregivers will be collected from the Fostering Connections web application (eg, total number of messages sent and received, number of messages read, content of the messages, and number of contacts with the FCFNs).

##### FCFN Feasibility, Acceptability, and Satisfaction: Evidence-Based Practice Attitude Scale-50

This 50-item scale was developed and validated with mental health service providers and assesses global attitudes toward the adoption of evidence-based practices [42].

##### FCFN Feasibility, Acceptability, and Satisfaction: FCFN Fidelity Forms

As part of intervention delivery, the FCFNs will rate the adherence to sessions (eg, activities completed and number of contacts) of youth and caregivers. The FCFNs will also complete their own feedback session forms after each of the six 60-minute sessions to document the occurrence of planned activities and content and the occurrence of additional activities (that might not have been part of the FCFN manualized intervention), as well as any aberrant events.

##### Exit Interviews With Youth and Caregivers

A subsample of 12 families or 24 participants (6 youths and 6 caregivers or 12 participants from each condition) will be invited to participate in an exit interview at the end of the 6-month intervention period to inform feasibility, acceptability, and satisfaction with the FCFN and standard of care (clinical case management services) conditions. Each participant will be offered a US $40 gift card (applicable to those who are allowed to receive it).

##### Exit Interviews With Foster Care Family Navigators

Up to 5 FCFNs will be invited to participate in an exit interview at the end of the pilot RCT study phase to provide more detailed feedback on their experiences of delivering the FCFN intervention and to inform future trials. Each participant will be offered a US $40 gift card (applicable to those who are allowed to receive it).

### Statistical Analysis

#### Quantitative Analysis

##### Overview

Analyses will be conducted using SAS 9.4 (SAS Institute Inc) [55]. Preliminary analyses will include an examination of descriptive statistics and distributions. Scaled psychometric measures (eg, the Barriers to Care Questionnaire) will be scored according to established algorithms and internal consistency reliability examined. Item-level missing data will be minimized through the programming of surveys; multiple imputation (PROC MI) will be used for item-level missing data if missingness is random. A unified statistical framework—generalized linear mixed models (GLMMs; PROC GLIMMIX)—will be used for most analyses. These models account for the clustering of participants and for unit-level missing data.

##### Cascade Outcomes

GLMM analyses of dichotomous outcomes (screening, treatment initiation, etc) will include intervention (FCFN group vs control group) as a fixed between-participants effect. Cox regression analysis (PROC PHREG) will be used to compare the interventions on time-to-event outcomes (eg, time to assessment) using a shared frailty model that accounts for clustering within pods. The potential mediators and mechanisms of change, measured longitudinally (at baseline and at 1, 3, and 6 months) only for FCFN intervention participants, will be initially examined for intervention impact using GLMMs that include a repeated within-participants time effect. The majority of the mediators are scaled variables, anticipated to have normal distributions, but final models and link functions will be chosen based on observed distributions. It will not be possible to test mediation without data from the control group. Therefore, we will identify potential mediators to be studied in the future trial by first determining which potential mediators change between baseline and month 1 or month 3 and then examining whether month 1 or month 3 values and changes between baseline and month 1 or month 3 are associated with cascade outcomes.

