### Study Objectives

This study will be the first to develop and test a foster care family navigator (FCFN) intervention for CWI youth that has the potential to significantly improve adolescent mental health disparities, particularly for racial and ethnic minoritized youth. The primary goal of the study is to assess the feasibility, acceptability, and preliminary impact of the FCFN intervention on the mental health services cascade of care (eg, screening, assessment, and treatment initiation) outcomes. Using a randomized controlled trial (RCT) design, we will randomize 80 families to receive either the FCFN intervention or standard of care (clinical case management services): 40 (50%) to FCFN and 40 (50%) to control. Qualitative exit interviews will inform the feasibility and acceptability of the services received during the 6-month period. Primary trial outcomes are mental health treatment initiation and engagement. Other pre- and postservice outcomes, such as proportion screened and time to screening, will also be evaluated.

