#### Randomization

Participants will be randomized (using a computer-generated randomization tool) to either the FCFN intervention group (40/80, 50%) or the standard of care group (40/80, 50%) directly after consent and completion of the baseline assessment.

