Potential limitations and design considerations include a partnering clinic that does not serve a sufficiently large sample size of CWI youth to be the sole site for the next phase of the large-scale trial. However, our investigators have existing research partnerships with other nearby large northern California counties that would allow us to expand and conduct large-scale FCFN intervention testing with other mental health clinics serving CWI youth using the same design approach as the pilot trial. Furthermore, sample size limitations may limit the current potential to analyze outcomes by those receiving the FCFN intervention as part of in-home services versus out-of-home placement and other demographic variables (eg, ethnoracial identity, gender, and socioeconomic status). Placement type and stability are important to consider in terms of intervention impact; thus, we will descriptively explore how outcomes may differ according to these variables to inform the future larger trial.

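### The claim that the mixed models account for unit-level missing data does not hold for treatment initiation and engagement as their model is described

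*Protocol article*

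**What the plan says.** All references are to the protocol article.

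- **Primary outcomes (Study Objectives).** "Primary trial outcomes are mental health treatment initiation and engagement". Under Cascade of Care Services, engagement is a single status for each youth: "whether the youth engaged in treatment (whether they had ≥6 weeks of treatment attendance". Table 1 defines being in treatment by the presence of a treatment start date.
- **Model family (Statistical Analysis, Overview).** Generalized linear mixed models (GLMMs) "will be used for most analyses", and "These models account for the clustering of participants and for unit-level missing data". Imputation is narrower: "multiple imputation (PROC MI) will be used for item-level missing data if missingness is random".
- **Model for the binary cascade outcomes (Cascade Outcomes).** The GLMMs "will include intervention (FCFN group vs control group) as a fixed between-participants effect". A repeated time effect is named only for the mediator models, which use navigator-arm participants alone.
- **Moderators.** Baseline variables such as sex, race and ethnicity, and symptoms are added singly to the cascade models, with interactions. They are therefore not part of the base model.
- **Data available.** Cascade data come from the electronic medical record in both arms, at baseline and 1, 3 and 6 months. Randomization follows the baseline assessment, so the Pediatric Symptom Checklist and placement type are in hand beforehand.

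**The concern.** A mixed model copes with a missing outcome by drawing on the same participant's other outcome records, or on covariates that explain both the missingness and the outcome. Initiation and engagement, as described, have neither. Imputing questionnaire items does not help either, because these outcomes are not questionnaire scores. The overview sentence therefore promises a protection that the primary analysis lacks.

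The article gives some reason to care. It describes placement instability as usual in this population. The average dependency process lasts 6 months, the same as follow-up. Contact differs by design: navigators hold sessions and check-ins, while control case managers seldom meet families in person. Ascertainment that differs by arm is therefore plausible, though the article neither reports nor predicts it. If it occurred, a reader relying on that sentence would believe it had been dealt with.

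**Working it through.** The article states no power, event rate or missingness rate, so there is no figure of its own to reproduce. Every rate below other than the 40 per arm is an assumption.

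**1. What the likelihood uses.** With one binary record per youth, the likelihood is a product over observed youths, each term depending on arm (and cluster). A youth with no status contributes a factor of 1. A cluster effect does not change this, since it carries no information on that youth's own outcome. The fit is a complete-case comparison. Each arm's observed proportion is unbiased only if missingness is unrelated to outcome within that arm.

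**2. Size of the possible bias, with no true effect.** Take a baseline factor split 50/50, with outcome probabilities y1 and y0 at its two levels, where logit(y) = −0.4 ± g/2. In control, a fraction r is missing regardless of the factor. In the navigator arm, a fraction 2r is missing at the y0 level and none at the y1 level, so r is missing overall in both arms.

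- Navigator observed proportion = [0.5·y1 + 0.5·y0·(1 − 2r)] / (1 − r)
- Control observed proportion = (y1 + y0)/2
- Spurious difference = (y1 − y0)·r / [2(1 − r)]

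Example: odds ratio 4.48 (g = 1.5) gives y1 = 0.587 and y0 = 0.240. With r = 0.3, the difference is 0.347 × 0.3/1.4 = 0.074.

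| Factor odds ratio | r = 10% | r = 20% | r = 30% |
|---|---|---|---|
| 1.65 | 0.007 | 0.015 | 0.026 |
| 2.72 | 0.013 | 0.030 | 0.051 |
| 4.48 | 0.019 | 0.043 | 0.074 |

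A simulation of 400,000 youths agreed within sampling error (0.009 to 0.075 over the same grid). Conditioning on the factor brought the difference to about 0. If the same mechanism acts in both arms, the arm-only difference is also about 0. For scale, the standard error of a difference between arms with full data and rates near 50% is √(2 × 0.25/40) = 0.112.

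**3. What baseline adjustment would add.** Simulated logistic regression, N = 80, arm log-odds 1.2, one standard-normal baseline predictor, 3,000 runs:

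| Predictor log-odds per SD | Power, arm only | Power, adjusted |
|---|---|---|
| 0 | 0.76 | 0.75 |
| 0.5 | 0.72 | 0.72 |
| 1.0 | 0.62 | 0.67 |
| 1.5 | 0.50 | 0.59 |

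At 1.2 per SD, a separate simulation of 4,000 runs gave 0.566 versus 0.632, a gain of 0.066; gains at this strength ranged from about 6 to 8 points between simulations. Type I error was 0.045 to 0.058 with or without adjustment.

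**4. Chance imbalance.** For a factor with prevalence 50%, a gap above 20 points means counts differing by more than 0.20 × 40 = 8. With X and Y each Binomial(40, 0.5), P(|X − Y| > 8) = 2·P(Binomial(80, 0.5) ≥ 49) = 0.057. The uncorrected normal approximation gives 0.074, which is too high.

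**The case against.** **The overview sentence is general.** It describes a framework used for most analyses and is sound for the longitudinal mediator models. It would also suit the cascade outcomes if the 1-, 3- and 6-month extracts were analysed as repeated measures. That is fair, but the Cascade Outcomes section does not say so and names a time effect only for the mediators. The sentence makes no exception for the primary outcomes.

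**Missingness may be small.** Outcomes come from the medical record, so questionnaire dropout does not remove them. Under Table 1, a youth with no start date would ordinarily count as not initiated rather than missing. This stands and limits the likely harm, although the article does not spell out the rule.

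**Baseline adjustment is optional.** A reader might infer that the primary model contains arm and nothing else, and that this is a mistake. The document does not support that. It says the models include arm, not that they exclude all else; clustering is also modelled, and covariate lists are commonly left to an analysis plan that is not shown. An arm-only randomized comparison keeps its type I error, and its confidence interval already allows for chance imbalance.

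**Placement is not called prognostic.** The Discussion says "Placement type and stability are important to consider in terms of intervention impact", which concerns modification of the effect, and proposes descriptive exploration. Baseline placement also cannot capture later moves, so adjusting for it would not by itself deal with youths who move and leave the record.

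**Conclusion.** The point holds for the missing-data statement. For initiation and engagement as described, the GLMM does not account for unit-level missing data; it drops the youth. This follows from the structure of the model and needs no assumed rate.

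The size of the consequence does rest on assumptions. If missingness follows a prognostic factor in one arm only, the spurious difference is about 1 to 2 points at 10% missing, 1 to 4 at 20% and 3 to 7 at 30%, for factor odds ratios of 1.65 to 4.48. It is near zero under no true effect if the mechanism is the same in both arms. It would be tempting to conclude that the trial's comparison will be biased; the documents do not show that.

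The lack of named covariates is not a defect. Adjustment is a cheap improvement worth roughly 0 to 7 power points for predictors of 0.5 to 1.2 log-odds per SD, and about 10 for stronger ones; the article gives no evidence on how strong its baseline variables are. The chance of an imbalance above 20 points in an evenly split factor is about 5.7%. Severity is modest, since the stated goal is feasibility, acceptability and preliminary impact.

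**What to change.** 1. Limit the overview sentence to the repeated-measures models.
2. For initiation and engagement, state that a youth who is in the medical record with no treatment start date counts as not initiated. Define when a status is truly unascertainable, and report the number by arm.
3. Treat unascertainable statuses as missing at random given arm and prespecified baseline covariates. Add a sensitivity analysis that departs from this assumption.
4. As an optional improvement, prespecify the primary model as arm plus a small number of baseline covariates already collected, for example placement type and one Pediatric Symptom Checklist score. Name the source of that score, since the measure comes from youth, caregiver and record. Show the arm-only result as a sensitivity analysis.

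The cost is a few sentences of analysis text, with no new data collection. Keeping the covariates few avoids sparse-data problems with 80 youths. If the analysis plan already covers items 2 to 4, only the overview sentence needs changing.

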### Hypotheses

We hypothesize that youth receiving the FCFN intervention will have increased rates of mental health treatment initiation and engagement compared with youth receiving standard of care. We will also explore hypothesized mechanisms of intervention impact (eg, navigator satisfaction, youth treatment motivation, and perceived barriers to care) as well as potential moderators (eg, sex, race, ethnicity, and out-of-home placement status).

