## Methods

### Study Design

Up to 5 FCFNs and 80 families (caregiver-youth dyads) will participate in the RCT to assess the preliminary impact of the FCFN intervention on mental health services use. CWI youth (in in-home or out-of-home placement) aged between 12 and 17 years as well as their caregivers will be referred for study participation at the point of referral from the child welfare system to a partnering mental health clinic (hereinafter referred to as the foster care mental health [FCMH] clinic) that specializes in serving foster care youth by linking them to specialty mental health services. Enrolled families will be randomized to either the FCFN intervention or standard of care. Enrolled CWI youth and their caregivers will complete a computerized set of questionnaires (on a tablet device, mobile phone, PC, or laptop computer) at baseline, midintervention (1-month after baseline), and at 3 and 6 months after randomization.

The trial has been registered with ClinicalTrials.gov (NCT04506437).

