##### Moderators

We will examine potential moderators (eg, sex, gender, race and ethnicity, and mental health symptoms) of intervention impact by adding the potential moderators one at a time, given the modest sample size, to the models used to examine cascade outcomes and mediators. Analyses of cascade outcomes will include moderator × intervention interactions, and analyses of mediators will include moderator × time interactions.

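### The analysis section says mediators are measured only in the FCFN arm, the measures section schedules them in both arms, and a one-arm time effect cannot show intervention impact on either reading

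*Protocol article*

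**What the plan says.** All references are to the protocol article.

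- **Cascade Outcomes (Statistical Analysis).** The candidate mediators are described as "The potential mediators and mechanisms of change, measured longitudinally (at baseline and at 1, 3, and 6 months) only for FCFN intervention participants". They "will be initially examined for intervention impact using GLMMs that include a repeated within-participants time effect". The section then states: "It will not be possible to test mediation without data from the control group". As a substitute it screens candidates for a later trial in two steps: which of them change from baseline to month 1 or 3, and whether the month 1 or 3 values and changes are associated with cascade outcomes.
- **Moderators.** For cascade outcomes the models use moderator × intervention. For mediators the text reads "and analyses of mediators will include moderator" × time, with no arm term.
- **Measures, Overview.** "Youth and caregivers in both conditions will each complete the electronic study assessment at baseline and at 1, 3, and 6 months". It adds a default: "Unless it is specifically noted, all of the following measures will be collected from youth and caregivers across both conditions".
- **Study Design.** "Enrolled CWI youth and their caregivers will complete a computerized set of questionnaires" at baseline, 1, 3 and 6 months. This covers enrolled families without distinction of arm.
- **Hypotheses.** "We will also explore hypothesized mechanisms of intervention impact (eg, navigator satisfaction, youth treatment motivation, and perceived barriers to care").
- **Individual measures.** The Barriers to Care Questionnaire and the Motivation for Youth's Treatment Scale have no arm restriction. The System Usability Scale (SUS) is expressly limited to the intervention group. The Navigation Satisfaction Tool (NAVSAT) has no restriction in words, but its items ask about a navigator.

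**The concern.** There are two linked problems.

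First, the sections disagree on whether control families supply mediator data. The answer decides whether the reason given for not testing mediation is true.

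Second, the plan examines intervention impact on mediators through change over time in one randomised arm. Families enter at referral to a mental health clinic, and controls receive case management. Motivation and perceived barriers could shift with time since referral, regression to the mean or usual services, without any navigator effect. One-arm change contains all of these. The opposite error is also possible: a mediator that FCFN holds steady while controls worsen shows no change and would fail the first screening step.

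What is at stake is which mechanisms are taken into the larger trial, and whether the report describes uncontrolled change as an effect of the intervention.

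**Working it through.** **Step 1. Which measures are affected**

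| Mechanism named under Hypotheses | Scale | Arm note in Measures | Arms under the overview's default |
|---|---|---|---|
| Youth treatment motivation | Motivation for Youth's Treatment Scale | none | both |
| Perceived barriers | Barriers to Care Questionnaire | none | both |
| Navigator satisfaction | NAVSAT | none, but navigator-specific by content | FCFN only makes sense |

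The conflict with Cascade Outcomes therefore rests on motivation and barriers. Nothing in the article reconciles it.

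**Step 2. The one-arm test on each reading**

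Write the mean change in FCFN as drift + intervention effect, and in controls as drift alone (drift includes usual care). The one-arm time effect estimates the sum. Only the difference between arms (intervention × time) isolates the second term. This holds whether or not control data are collected. Moderator × time in one arm has the same limit: it shows whose scores change more, not for whom the navigator works better.

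**Step 3. Illustration of the first screening step**

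The article gives no figure to reproduce. Inputs:

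- n = 40 in FCFN (Randomization section); n = 32 as an assumed 20% loss
- two-sided 5% level: assumed
- intervention effect: zero by construction
- drift g, in baseline SD units and common to both arms: assumed 0.2 to 0.5
- correlation r between baseline and follow-up: assumed 0.5 or 0.7

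SD of change = √(2(1 − r)), which is 1.00 at r = 0.5 and 0.775 at r = 0.7.
Non-centrality = g√n / SD of change. For g = 0.2, n = 40, r = 0.5: 0.2 × 6.325 / 1.00 = 1.265.

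Probability of a significant one-arm change (noncentral t, n − 1 degrees of freedom):

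| g | n=40, r=0.5 | n=40, r=0.7 | n=32, r=0.5 | n=32, r=0.7 |
|---|---|---|---|---|
| 0.2 | 0.235 | 0.357 | 0.195 | 0.293 |
| 0.3 | 0.457 | 0.666 | 0.376 | 0.565 |
| 0.4 | 0.694 | 0.890 | 0.592 | 0.808 |
| 0.5 | 0.869 | 0.978 | 0.782 | 0.943 |

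Simulation of the first column gave 0.234, 0.459, 0.693 and 0.871. A two-arm intervention × time test stays near 5% throughout, because common drift cancels.

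**Step 4. What a two-arm comparison could detect**

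Detectable standardised difference at 80% power = (1.960 + 0.842)√(2/n), multiplied by √(1 − r²) with baseline adjustment.

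- 40 per arm: 0.63 SD unadjusted; 0.54 at r = 0.5; 0.45 at r = 0.7
- 32 per arm: 0.70, 0.61 and 0.50 SD

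Power for a 0.5 SD difference, unadjusted, is 61% with 40 per arm and 52% with 32. The comparison is feasible but exploratory.

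**The case against.** **The step is openly exploratory.** The primary outcomes are treatment initiation and engagement, compared between randomised arms. The plan concedes that mediation is not tested and presents the step as choosing candidates for a later trial. This stands, and it limits severity. It does not make a one-arm change evidence of intervention impact.

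**The analysis section may be the accurate one.** A reader might infer that control data certainly exist and that the statement about mediation is simply false. The article does not support that. The analysis section is specific and gives a reason, while the overview states a general default. That default also fails to flag NAVSAT, which controls could not sensibly complete. The missing arm notes on motivation and barriers are evidence of collection in both arms, not proof.

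**There is a second filter.** A reader might take 23% to 87% as the rate at which wrong mechanisms go forward. It is not: those figures cover only the first step and rest on assumed drift and correlation. The second step, association with cascade outcomes, is also uncontrolled but is not quantified here.

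**The sample is small.** With 40 per arm, leaving formal mediation to the larger trial is a legitimate pilot choice. That stands. Low power is no reason, however, to give up a randomised comparison of mediators where the data exist.

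**Conclusion.** The point holds at moderate severity. Cascade Outcomes conflicts with the Measures overview and Study Design on whether motivation and barriers are measured in controls, and the article does not settle which is right. If the overview is right, the stated reason for not testing mediation fails for those two scales and randomised control data go unused. If Cascade Outcomes is right, the overview misdescribes data collection. On both readings the intervention-impact label on a one-arm time effect is unsupported, and the moderator × time models for mediators inherit the problem.

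The size depends on drift and correlation that the article does not give. For an assumed common drift of 0.2 to 0.5 SD and 40 participants, false signals at the first step run from about 23% to 87% at r = 0.5, and from about 36% to 98% at r = 0.7, against a nominal 5%. With no drift the rate is 5%.

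Single-arm analysis is appropriate for navigator satisfaction and the SUS. The primary cascade comparisons, and the moderator × intervention models for them, are unaffected. This is not a flaw that must be fixed before the trial's main result can be trusted.

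**What to change.** 1. Check what is actually collected from control families, then reconcile Cascade Outcomes with the Measures overview and Study Design. Mark NAVSAT as intervention-only if that is the practice.
2. Where control data exist (motivation and barriers, if the overview is right), fit the mediator GLMM on both arms with baseline adjustment, and name intervention × time as the test of intervention impact. Correct the statement that mediation is untestable for lack of control data. Any mediation or moderation analysis of these measures is optional and should be labelled exploratory, given 40 per arm.
3. If control data are not collected, correct the Measures overview.
4. For measures that exist only in FCFN, keep the one-arm analysis as descriptive. Remove the intervention-impact wording there and from the matching moderator × time analyses.

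Cost: if control data are collected, wording and a small change to the model. If they are not, wording only; recruitment began in August 2020, so new wording cannot recover control assessments that were never made, and the one-arm analysis stays descriptive.
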